### Randomization

In this study, a total of 210 patients with mild-to-moderate AD will be randomly allocated to either treatment group or control group in a 2:1 ratio. We will apply cluster randomization with the combined blocks of 4 and 6 to ensure a balanced group allocation. Randomization sequences will be computer-generated by an independent statistician using SAS software (version 9.4; SAS Institute Inc). Randomization was centralized across all 10 hospitals, with 21 random numbers assigned to each hospital. Allocation concealment will be maintained through sequentially numbered, opaque envelopes securely stored with restricted access at the clinical research center of Shanghai Skin Disease Hospital.

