## Methods and analysis

### Study design

This study is a multicenter, randomized, double-blind, placebo-controlled trial to evaluate the efficacy of Fuzhiqing ointment in treating mild-to-moderate AD. The study design adheres to the SPIRIT (Standard Protocol Items: Recommendations for Interventional Trials) statement (16). A total of 210 patients with mild-to-moderate AD will be recruited in 10 hospitals between September 2025 and February 2026. Participating sites include Shanghai Skin Disease Hospital, Yueyang Hospital of Integrated Traditional Chinese and Western Medicine affiliated to Shanghai University of Traditional Chinese Medicine, China-Japan Friendship Hospital, Hangzhou Third People’s Hospital, Chongqing Traditional Chinese Medicine Hospital, The Second Affiliated Hospital of Xi’an Jiaotong University, Beijing Hospital of Traditional Chinese Medicine, Guangdong Provincial Hospital of Chinese Medicine, Peking University Third Hospital and Hubei Provincial Hospital of Traditional Chinese Medicine. A total of 210 patients with mild-to-moderate AD will be randomly allocated in a 2:1 ratio to the treatment group (urea vitamin E cream and Fuzhiqing ointment; *n* = 140) or the control group (urea vitamin E cream and placebo Fuzhiqing ointment; *n* = 70). Each patient in both groups will receive two treatment sessions per day for 2 weeks, followed by a 4-week follow-up period. The study flowchart is presented in Figure 1.

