### Sample size

The sample size was calculated based on the EASI50 achievement rate at week 2, which was defined as the proportion of patients who achieved ≥50% improvement in Eczema Area and Severity Index (EASI) score from baseline to week 2. According to previous evidence, we assume that the EASI50 achievement rate at week 2 was 60% in the treatment group and 30% in the control group (18). The sample size calculation for a 2:1 randomization design performed in PASS 15.0 (NCSS Statistical Software) indicates that 116 patients in the treatment group and 58 patients in the control group need to recruit with a 2-tailed *α* level of 0.05 and a statistical power of 80%. Considering a dropout rate of 10 and 10% multicenter effect, the final enrollment targets are 140 patients in the treatment group and 70 patients in the control group.

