#### Secondary outcomes

The secondary outcome indicators include the EASI and Numerical Rating Scale (NRS) evaluated at week 1, 2, and 6; Investigator’s Global Assessment (IGA), Dermatology Life Quality Index (DLQI) and Atopic Dermatitis Control Tool (ADCT) evaluated at weeks 1 and 2 (20, 21). The comprehensive study schedule is detailed in Table 2, demonstrating the specific evaluation time-point for each indicator.

**Table 2 tab2:** Study schedule of the Fuzhiqing ointment clinical trial (6 weeks).

Indicator	Baseline	Treatment		Follow-up
	Visit 1 (week 0)	Visit 2 (week 1)	Visit 3 (week 2)	Visit 3 (week 6)
Informed consent	✓	—^a^	—	—
Demographic features	✓	—	—	—
Medical history	✓	—	—	—
Physical examination	✓	—	—	—
Blood biochemistry	✓	—	✓	—
Urine pregnancy	✓	—	✓	—
Inclusion/exclusion criteria check	✓	—	—	—
Randomization	✓	—	—	—
EASI^b^	✓	✓	✓	✓
NRS^c^	✓	✓	✓	✓
IGA^d^	✓	✓	✓	—
DLQI^e^	✓	✓	✓	—
ADCT^f^	✓	✓	✓	—
Concomitant medications	—	✓	✓	✓
Adverse events	—	✓	✓	✓

a Not applicable.

b EASI: Eczema Area and Severity Index.

c NRS: Numerical Rating Scale.

d IGA: Investigator’s Global Assessment.

e DLQI: Dermatology Life Quality Index.

f ADCT: Atopic Dermatitis Control Tool.

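### The stated blocks of 4 cannot hold the 2:1 ratio, and the term cluster randomisation contradicts the allocation of individual patients

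*Protocol article*

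**What the plan says.** The Randomization section says that 210 patients "will be randomly allocated to either treatment group or control group in a 2:1 ratio". The method follows: "We will apply cluster randomization with the combined blocks of 4 and 6 to ensure a balanced group allocation". The section adds "Randomization was centralized across all 10 hospitals", "with 21 random numbers assigned to each hospital", and says that concealment relies on numbered opaque envelopes held at one centre.

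The Sample size section gives the targets: "the final enrollment targets are 140 patients in the treatment group and 70 patients in the control group". The Study design section repeats that patients "will be randomly allocated in a 2:1 ratio to the treatment group". Table 2 has a row "Randomization" that is ticked only at the baseline visit.

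The article does not say whether the list is stratified by hospital, how a block of 4 is divided, or in what proportion the two block sizes are used.

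**The concern.** Blocking serves to hold the allocation ratio as patients accrue. A block size that cannot contain the ratio cannot do this. If the list was built as described, its overall ratio may differ from 2:1, and nobody could reproduce or audit it from the text. If it was built differently, the article misreports it.

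Cluster randomisation means allocating groups, such as hospitals, instead of patients. Using that name in the section that defines the unit of allocation tells the reader that the trial has a different design from the one set out elsewhere.

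The matter is live. The article's Results section says that recruitment began in February 2025 (the Study design section says September 2025), and the centralisation of the randomisation is reported in the past tense. A list may therefore already be in use.

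**Working it through.** **Inputs.** Ratio 2:1, block sizes 4 and 6, 10 hospitals and 21 numbers per hospital (Randomization); arm targets of 140 and 70 (Sample size).

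**1. Totals.** 10 × 21 = 210. 210 × 2/3 = 140 and 210 × 1/3 = 70. The totals agree with each other and with the ratio.

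**2. Ratio within a block.** The treatment share of a block is its size × 2/3, which must be a whole number.
- Block of 6: 6 × 2/3 = 4, so 4:2. This works.
- Block of 4: 4 × 2/3 = 2.67, so 2.67:1.33. This is impossible; the nearest splits are 3:1 and 2:2.

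**3. Overall ratio from complete blocks.** Let *a* be the number of 4-blocks and *b* the number of 6-blocks, with 4*a* + 6*b* = 210. The treatment target is (2/3)(4*a* + 6*b*) = 8*a*/3 + 4*b* = 140.
- 4-blocks at 3:1: treatment = 3*a* + 4*b*, which exceeds the target by *a*/3.
- 4-blocks at 2:2: treatment = 2*a* + 4*b*, which falls short of it by 2*a*/3.

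The deviation is zero only when *a* = 0, that is, with 35 blocks of 6. Examples where both sizes are used:

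| 4-blocks | 6-blocks | 4-blocks at 3:1 | 4-blocks at 2:2 |
|---|---|---|---|
| 3 | 33 | 141:69 | 138:72 |
| 21 | 21 | 147:63 | 126:84 |
| 51 | 1 | 157:53 | 106:104 |

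The article does not state the mix. The row with 21 of each is an illustration only.

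**4. Numbers per hospital.** 4*a* + 6*b* = 21 has no whole-number solution, because the left side is always even and 21 is odd. This matters only if blocks are to be complete within each hospital. If the 21 numbers are consecutive slices of one central list of 210, or if the last block is cut short, 21 can be reached, but balance within a hospital is then not guaranteed.

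**5. Unit of allocation.** Study design and Randomization both allocate patients, and Table 2 places randomisation at the baseline visit. If whole hospitals of 21 were allocated instead, the treatment arm would need 140/21 = 6.67 hospitals; the nearest division, 7 and 3, gives 147:63. Hospital-level allocation therefore does not fit the stated targets either.

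**6. Effect on precision.** The variance of a group difference, taking equal variance per patient, is proportional to 1/*n*₁ + 1/*n*₂.
- 140:70: 1/140 + 1/70 = 0.02143
- 147:63: 1/147 + 1/63 = 0.02268
- 126:84: 1/126 + 1/84 = 0.01984

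Against 140:70, 147:63 loses about 5.5% of the information (1 − 0.02143/0.02268), and 126:84 gains a little.

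**7. A scheme that fits.** 3*a* + 6*b* = 21 is solved by 1×3 + 3×6, 3×3 + 2×6 and 5×3 + 1×6 (and by 7×3). Each gives 14:7 per hospital and 140:70 over 10 hospitals.

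**The case against.** The best defence is that the totals are still attainable. If the 4-blocks do not all share one split, two at 3:1 and one at 2:2 give 8:4; with 33 blocks of 6 (132:66) the list has 210 numbers at exactly 140:70. A reader might infer from the block sizes that 140:70 is out of reach, and that goes too far. What stands is narrower: no single 4-block keeps 2:1, and the article describes no such compensating scheme.

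The point about 21 per hospital is also conditional. The randomisation is called central, and the article states neither stratification by hospital nor a target of 14:7 in each. A reader might take 14:7 as planned, but that figure is only 2:1 applied to 21.

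The word cluster invites the strongest reading: that hospitals are the units, that patient-level tests are invalid, and that the effective sample size shrinks. The documents do not support this. Apart from that one word, every description is of individual allocation, so a design effect would size a trial that nobody has described. Nor is the 10% multicentre allowance in the Sample size section defined as a cluster correction. The word is most likely a slip for block or centre-stratified randomisation.

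Finally, the harm to the analysis is small. Random allocation stays unbiased at 147:63 or 126:84. This is correct, and it limits the point to whether the allocation rule is accurate and reproducible.

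**Conclusion.** The concern holds in a limited form. The randomisation rule is wrong as written: blocks of 4 cannot keep a 2:1 balance, and the cluster label contradicts the patient-level allocation in the Study design section, the Randomization section itself and Table 2. Both conclusions follow from the text and simple arithmetic, without assumptions.

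The size of any departure from 140:70 is unknown. The figures 147:63 and 126:84 rest on an assumed equal mix and one fixed split of the 4-blocks. The conflict with 21 numbers per hospital rests on blocks being complete within each hospital.

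The documents cannot show whether the list itself is faulty or only its description. The sentence needs correcting in either case; the list needs attention only if 4-blocks were really used.

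**What to change.** The order matters, because a list may already be in use.

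1. **Check first.** The independent statistician inspects the list already generated, without revealing allocations to the blinded team.
2. **If the block sizes were multiples of 3,** correct the sentence: individual 2:1 randomisation, the actual block sizes, and whether the list is stratified by hospital. Delete the word cluster.
3. **If 4-blocks were used,** document how they were split, and report the actual scheme and ratio. Delete the word cluster here too.
4. **If no list is in use yet,** generate one with permuted blocks of 3 and 6 within hospital, in random order, for example 1×3 + 3×6 or 3×3 + 2×6. This gives exactly 21 numbers and 14:7 per hospital, and 140:70 overall. The same blocks can replace unused numbers where the blinded supplies allow. In that case 2:1 is restored only for the new part, and the overall ratio must be reported as it falls.

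The cost is a list check, a corrected sentence and possibly the re-issue of unused numbered envelopes and supplies. No extra patients are needed.

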### Blinding

In this study, both of patients with mild-to moderate AD and dermatologists (investigators) will be blinded to the treatment allocation. Furthermore, the outcome assessors, data collectors and statistician responsible for data analysis are also unaware of the group assignment during the trial period to prevent bias.

### Interventions

Patients in the treatment group will receive twice daily treatment sessions of urea vitamin E cream and Fuzhiqing ointment for 2 weeks. The detailed composition of Fuzhiqing ointment is shown in Table 1. To ensure the correct application of urea vitamin E cream and Fuzhiqing ointment, dermatologists will instruct patients to apply Fuzhiqing ointment first and urea vitamin E cream at least 5 min later to the affected area and instruct patients that one knuckle length of urea vitamin E cream and Fuzhiqing ointment should be used to cover no more than 1% of the body surface area. Moreover, the application of Fuzhiqing ointment and urea vitamin E cream should be followed by 1 to 3 min of finger massage to promote absorption.

**Table 1 tab1:** The detailed composition of Fuzhiqing ointment.

Component	Pharmacological activity
Tinospora root	antibacterial; anti-inflammatory; antiviral; anti-tumor; immunomodulatory
Rhubarb	antibacterial; anti-inflammatory; anti-tumor; hemostatic; antioxidant
Golden cypress	antibacterial; anti-inflammatory; antiviral; anti-fungal; antioxidant
*Ardisia crenata*	relieves cough and phlegm; antibacterial; anti-inflammatory; antiviral; anti-tumor; pain relief; promoting blood circulation for removing blood stasis
Chinese violet	antibacterial; anti-inflammatory; antiviral; anti-tumor; immunomodulatory; antioxidant
Wild chrysanthemum	antibacterial; anti-inflammatory; antiviral; immunomodulatory; antioxidant; cardiovascular protection
Hemsleya amabilis	antibacterial; anti-inflammatory; anti-tumor; antipyretic; analgesic
*Sophora flavescens*	antibacterial; anti-inflammatory; antiviral; anti-tumor; anti-arrhythmic; relieving asthma; anti-allergy
Paris polyphylla	antibacterial; anti-inflammatory; antiviral; anti-tumor; immunomodulatory; hemostatic; sedative; analgesic
Airpotato yam	antibacterial; antiviral; anti-tumor; anti-thyroid; hemostatic
Turmeric	anti-inflammatory; anti-tumor; antioxidant; liver and gallbladder protection; regulate blood lipids; anti-atherosclerotic
*Sanguisorba officinalis*	antibacterial; anti-inflammatory; hemostasis; antioxidant; anti-anaphylaxis; promotes wound healing and contraction; protects gastrointestinal mucosa (anti-ulcer)
Kuding tea	antibacterial; anti-inflammatory; regulate blood lipids; regulate blood pressure; antioxidant; anti-aging; anti-atherosclerotic
Borneol	antibacterial; anti-inflammatory; pain relief; local anesthesia; promote blood–brain barrier permeability; promote drug absorption
Menthol	cooling; pain relief; itch relief; promotes local blood circulation

Patients in the control group will also receive twice daily treatment sessions of urea vitamin E cream and placebo Fuzhiqing ointment for 2 weeks. The placebo Fuzhiqing ointment is made using guar gum as a thickening agent, caramel color as a coloring agent, and purified water as a filler. Therefore, it has the consistency of a traditional Chinese medicinal ointment but does not contain any active ingredients, and as such, does not have therapeutic effects. The placebo Fuzhiqing ointment is produced and provided by the same company, which maintains complete consistency with the Fuzhiqing ointment in terms of appearance, weight, color, odor, and package. The medication guidance and application of placebo Fuzhiqing ointment and urea vitamin E cream in the control group are completely consistent with that in the treatment group. In this study, no additional treatment is permitted during the study. Emergency interventions require documentation in detail and will result in the withdrawal of participation.

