### Outcomes

#### Primary outcome

The primary outcome indicator in this study is the EASI50 achievement rate at week 2. The EASI50 achievement rate is defined as the proportion of patients with mild-to-moderate AD who achieved ≥50% improvement in EASI score from baseline to week 2.

The EASI score includes the affected body surface area score (A) and clinical features score (B) of the head and neck, trunk, upper limbs, and lower limbs (19). (A) involves evaluating the percentage of affected body surface area (BSA) for each part. The percentage of affected BSA for each region is scored on a scale of 0–6: 0 (0%), 1 (<10%), 2 (10–19%), 3 (20–49%), 4 (50–69%), 5 (70–89%), and 6 (90–100%). (B) assesses four key clinical features, including erythema (E), edema/papules/infiltration (I), excoriation (Ex), and lichenification (L). Each feature is scored based on severity, ranging from 0 to 3 points (0 = none, 1 = mild, 2 = moderate, 3 = severe). The EASI score is calculated by multiplying the product of (A) and (B) with regional weighted coefficient (0.1–0.4) and then summing across all regions. The total score of EASI ranges from 0 to 72 points, with higher scores indicating greater severity. According to the EASI score, the skin lesion condition of AD patient is considered as mild (0–7 points), moderate (7–21 points), or severe (>21 points). In this study, the EASI score will be estimated at baseline (week 0), week 1, week 2, and week 6.

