### Safety assessment

In this study, patients with mild-to-moderate AD will be informed of the risks that may arise in the study before signing the informed consent form. We define adverse events as unintended signs, symptoms, or diseases occurring after treatment that are not necessarily related to the intervention. The occurrence of any adverse events will be accurately recorded in the CRF. In this study, appropriate treatment will be provided by dermatologists when encountering adverse events, the adherence condition of AD patients and the adverse events will be recorded. Meanwhile, liver and kidney function test for all participants and urine pregnancy test only for female participants will be conducted at baseline and week 2 for safety evaluation.

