### Statistical analysis

In this study, analysis will be performed by applying SAS 9.4 statistical package. Normally distributed quantitative variables will be summarized as mean and standard deviation (SD), while those with skewed distributions will be presented as median and interquartile range (IQR). The Student *t*-test will be used for inter-group comparison of quantitative variables with normal distribution, while the Wilcoxon rank-sum test will be employed for quantitative data with skewed distribution. The repeated measurement data will be analyzed by repeated measure analysis of variance. Categorical variables will be reported as frequencies and proportions (%), with group differences assessed using chi-square tests or Fisher’s exact tests. In this study, data analysis will adhere to the intention-to-treat (ITT) principle, including all randomized patients regardless of protocol adherence or study completion (25). Missing data will be handled under the missing-at-random assumption using sequential regression multiple imputation, which imputes missing values through regression models for each variable conditional on the other variables (26). Additionally, data analysis will be conducted on both the full analysis set (FAS) and the per-protocol set (PPS), and a *p*-value less than 0.05 (two tailed) is considered as statistically significant.

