This study is subject to several limitations. First, participant recruitment is restricted to individuals with mild-to-moderate AD, enhancing internal validity while potentially limiting the generalizability of findings to broader populations. Second, the protocol mandates a 2-week active treatment phase followed by a 4-week observational follow-up period, which limits the observation of long-term effects of Fuzhiqing ointment, as well as its efficacy of diseases recurrence prevention in patients with AD. Third, differences of climate (temperature, humidity, ultraviolet radiation, seasonal changes), lifestyle habits (high-fatty food consumption, high-calorie diets, tobacco smoking, alcohol drinking) and other extrinsic factors (cultural difference, occupational exposure, etc.) in the 10 selected hospitals may cause information bias. Fourth, patients in this study will be instructed not to use any additional treatment for AD which might induce a relatively high rate of withdrawal.

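### Emergency intervention ends trial participation, so patients withdrawn before week 2 lose the primary endpoint and the only follow-up laboratory test, and EASI50 is imputed under missing at random

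*Protocol article*

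**What the plan says.** The Interventions section bars additional treatment during the study and then sets the consequence of an emergency: "Emergency interventions require documentation in detail and will result in the withdrawal of participation".

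The assessments that this rule touches are fixed elsewhere in the article:

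- Primary outcome: "The primary outcome indicator in this study is the EASI50 achievement rate at week 2".
- Safety assessment: "liver and kidney function test for all participants and urine pregnancy test only for female participants will be conducted at baseline and week 2". Table 2 agrees, with blood biochemistry at baseline and week 2 only.
- Table 2 schedules adverse event review at weeks 1, 2 and 6.

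On analysis, the Statistical analysis section follows the intention-to-treat principle, "including all randomized patients regardless of protocol adherence or study completion". It adds: "Missing data will be handled under the missing-at-random assumption using sequential regression multiple imputation".

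Some information on a withdrawn patient is kept. Interventions asks for detailed documentation of the emergency measure, Safety assessment has any adverse event entered in the CRF, and Withdraw and dropout has the reason for leaving recorded.

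**The concern.** The rule ends participation, not just use of the ointment. Stopping study drug and leaving the trial are different events. After the first, the week 2 visit can still take place; after the second, as the sentence reads, it does not. The article therefore creates missing primary endpoint data by its own rule, in patients selected by a clinical event after randomization.

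The intention-to-treat statement governs who is analysed. It cannot restore a value that was never collected. The gap is filled by imputation under missing at random, which assumes that, given the observed data, the missing outcomes resemble those of patients who were seen. If the emergency measure was urgent treatment for worsening dermatitis, withdrawal is itself a sign of poor response, and the assumption is then at its weakest.

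Safety is affected too. A patient who needed urgent care would not have the single scheduled follow-up test of liver and kidney function, or the remaining adverse event visits.

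**Working it through.** **Step 1: what a withdrawn patient loses.** Table 2 gives one post-baseline EASI that defines the primary endpoint (week 2), one post-baseline blood test (week 2) and three adverse event visits (weeks 1, 2 and 6). If no assessment follows withdrawal:

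| Withdrawn | Week 2 EASI50 | Follow-up blood test | Adverse event visits lost |
|---|---|---|---|
| Before the week 1 visit | lost | 1 of 1 lost | 3 of 3 |
| Between weeks 1 and 2 | lost | 1 of 1 lost | 2 of 3 |
| After week 2 | kept | kept | 1 of 3 |

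Anyone withdrawn before week 2 thus loses the primary endpoint, the only post-baseline laboratory test and at least two of the three adverse event visits.

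**Step 2: what could happen to the primary estimate.** The article gives no figure for emergency interventions, so this step is an illustration.

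Inputs from the article:
- The Sample size section states: "we assume that the EASI50 achievement rate at week 2 was 60% in the treatment group and 30% in the control group".
- The planned arms are 140 and 70.
- The dropout allowance is 10%.

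Assumptions of this review:
- 10% of each arm is withdrawn for an emergency intervention before week 2.
- All of them are true non-responders.
- Imputation reproduces the completers' rate in the same arm.

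Responders at the design rates: 0.60 × 140 = 84 and 0.30 × 70 = 21. With nobody withdrawn, the difference is 84/140 − 21/70 = 60.0% − 30.0% = 30.0 points.

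With *a* treatment and *b* control non-responders withdrawn, the estimate becomes 84/(140 − *a*) − 21/(70 − *b*).

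- 10% of each arm (*a* = 14, *b* = 7): 84/126 − 21/63 = 66.7% − 33.3% = **33.3 points**, an overstatement of 3.3.
- The same total of 21, more in control (*a* = 7, *b* = 14): 84/133 − 21/56 = 63.2% − 37.5% = **25.7 points**, an understatement of 4.3.

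The sign therefore depends on the split by arm, which is unknown. If withdrawn patients respond like completers, the error is zero. If week 1 EASI is available and enters the imputation model, the error is smaller than shown.

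**The case against.** The strongest objection is that this rests on one sentence of a condensed article. An emergency intervention is not defined, and an early termination visit or continued follow-up may be set out in the full protocol. The Follow-up section also says in general terms that all patients are followed for six weeks. Part of this stands: the missing detail of an early termination visit is not a finding. But the sentence is not an omission. It states a mandatory consequence, and general schedule wording does not override it. If the full protocol does keep these patients under observation, the article misstates it and the sentence still needs correcting.

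Other objections limit the point:

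- *Frequency.* The Discussion warns that "patients in this study will be instructed not to use any additional treatment for AD which might induce a relatively high rate of withdrawal". A reader might infer that many emergency withdrawals are expected. The text does not say so: it concerns the ban on extra dermatitis treatment, and patients may also leave by choice.
- *Safety.* A reader might infer that safety information on these patients is lost altogether. It is not: events, the emergency measure and the reason for leaving are recorded up to withdrawal. What goes is the scheduled follow-up and the week 2 test.
- *Size.* Placing all 21 assumed withdrawals in one arm gives 84/140 − 21/49 = 17.1 points, or 84/119 − 21/70 = 40.6. These are extremes with no basis in the article. For control, 21 of 70 is 30% of the arm. They also set aside the stated method, which conditions each imputed value on the other variables; week 1 EASI, where recorded, would be one of them.
- *The remedy.* A week 2 EASI taken after urgent treatment may reflect that treatment. Collecting it without a rule for counting it could replace one bias with another. This objection is sound, and the change proposed must include such a rule.

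**Conclusion.** The point holds in a limited form. The article sets a rule that, followed as written, removes the primary endpoint, the only post-baseline liver and kidney test and the scheduled follow-up of the triggering event for any patient withdrawn before week 2. It then imputes EASI50 under an assumption that is doubtful if the intervention was given for worsening dermatitis.

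The size for the trial is unknown: the number of such patients, the split by arm and the direction of bias cannot be derived. The example of 33.3 instead of 30.0 points rests on three assumptions: 10% withdrawn in each arm, all non-responders, and imputation at the completers' rate. A reader might infer that the treatment effect will be exaggerated, but an uneven split can move the estimate the other way. The case for change is that the loss is avoidable and that a week 2 value not collected cannot be recovered later.

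**What to change.** In Interventions, replace the withdrawal rule with three statements:

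1. After an emergency intervention, study treatment is discontinued where needed.
2. The patient stays in the scheduled week 1, 2 and 6 assessments, including the week 2 liver and kidney test, unless consent is withdrawn.
3. EASI50 after emergency treatment for dermatitis is counted by a stated rule, for example as non-response in the primary analysis, with the observed week 2 value used in a sensitivity analysis.

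The cost is a wording amendment and a few visits from patients who are off treatment. The visits, tests and CRF pages already exist.
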